## Abstract

**Background:**

Suicidal thoughts are common, causing distress for millions of people all over the world. However, people with suicidal thoughts might not access support due to financial restraints, stigma or a lack of available treatment offers. Self-help programs provided online could overcome these barriers, and previous efforts show promising results in terms of reducing suicidal thoughts. This study aims to examine the effectiveness of an online self-help intervention in reducing suicidal thoughts among people at risk of suicide.

The Danish Self-help Online against Suicidal thoughts (SOS) trial is a partial replication of a previously conducted Dutch trial.

**Methods and design:**

A randomized, waiting-list controlled trial with 1:1 allocation ratio will be carried out. A total of 438 people with suicidal thoughts will be recruited from the Danish suicide hotline, The Lifeline’s, website and allocated to the intervention condition (*N* = 219) or the control condition (*N* = 219).

The intervention condition consists of a 6-week, Internet-based self-help therapy intervention. The format of the intervention is self-help, but the participants can be guided by the trial manager. The control condition consists of a waiting-list assignment for 32 weeks.

The primary outcomes are frequency and intensity of suicidal thoughts. Secondary outcome measures include depressive symptoms, hopelessness, worrying, quality of life, costs related to health care utilization and production loss. Number of deliberate self-harm episodes, suicides and deaths will, as well as the participant’s evaluation of the intervention and the experience of negative effects, be investigated. Assessments will be conducted over the intervention website through self-report questionnaires at baseline, 2 weeks, 4 weeks, 6 weeks and 32 weeks (6 months post intervention).

**Discussion:**

If we find the intervention to be linked to reductions in suicidal thoughts, this will strengthen the evidence that online self-help interventions are relevant tools for people with suicidal thoughts.

**Trial registration:**

ClinicalTrials.gov, NCT02872610. Registered on 9 August 2016.

**Electronic supplementary material:**

The online version of this article (doi:10.1186/s13063-017-1794-x) contains supplementary material, which is available to authorized users.

## Background

The World Health Organization estimates that suicide accounts for over 800,000 deaths each year [1] and the lifetime prevalence of suicidal ideation is found to be 9.2%; i.e., in one in ten persons [2].

Different support options exist for people with suicidal thoughts. In Denmark, people at risk of suicide can receive free specialized psychosocial therapy in Suicide Prevention Clinics [3]. Some of these clinics have been operating since 1992, and the treatment seems to be effective [3]. Another support option is The Lifeline which provides free and anonymous support online and via telephone [4]. However, even in a high-income country like Denmark with various support options, the relatively stable suicide rate over the last 10 years indicates that not all people with suicidal thoughts seek or benefit from the existing support options. Internet-based therapy is still at a very early stage in Denmark. In 2016 only a couple of studies in Denmark were investigating the effect of the few Internet-based therapy programs that exist, but findings from other countries indicate that clinically and cost-effective online treatment options exist for depression and anxiety disorders [5, 6]. A Dutch randomized controlled trial found that an online self-help intervention for people with suicidal thoughts was effective in lowering suicidal thoughts and cost-effective [7, 8].

The objective of the Danish Self-help Online against Suicidal thoughts (SOS) trial is to examine whether an Internet-based self-help intervention, provided to people with suicidal thoughts, is superior to a waiting-list control condition in reducing suicidal thoughts. Key secondary outcomes of this study cover psychological wellbeing as well as costs related to health care utilization and production loss.

The study is a partial replication of the aforementioned Dutch trial [7]. While the previous trial excluded people with severe suicidal thoughts and did not extend the follow-up period to post treatment, the Danish trial aims to address these issues.

## Methods and design

### Design

The SOS trial is designed as a randomized, controlled trial with a waiting-list control and with a 1:1 allocation ratio.

The primary hypothesis is that the intervention is superior to the control condition in reducing suicidal thoughts using the Beck Scale for Suicide Ideation at post test (6 weeks). Our secondary hypothesis is that the effect will be maintained at 6-month follow-up and that the program will be effective in improving the participant’s psychological wellbeing at post test and at follow-up. Table 1 shows the entries to the World Health Organization Trial Registration Data Set.

**Table 1 Tab1:** World Health Organization Trial Registration Data Set

Data category	Information
Primary registry and trial identifying number	ClinicalTrials.gov NCT02872610.
Date of registration in primary registry	18 August 2016
Secondary identifying number	TrygFonden 106690
	The Research Ethics Committee of the Capital Region of Denmark H-15002490
Source(s) of monetary or material support	TrygFonden reference number 106690
Primary sponsor	[name], Mental Health Centre Copenhagen
Contact for public queries	CM: [contact]
	MN: [contact]
	AE: [contact]
Contact for scientific queries	CM, MN, AE [contact]
	[contact]
	[contact]
	Mental Health Centre Copenhagen
Public title	The Self-help Online against Suicidal thoughts (SOS) trial – a Danish randomized controlled waiting-list trial for people with suicidal thoughts
Scientific title	The Self-help Online against Suicidal thoughts (SOS) trial – a Danish randomized controlled waiting-list trial for people with suicidal thoughts
Countries of recruitment	Denmark
Health condition(s) or problem(s) studied	Suicidal thoughts
Intevention(s)	An Internet-based self-help intervention for people with suicidal thoughts
	Waiting-list control condition
Key inclusion and exclusion criteria	Ages eligible for study: ≥18 years; sexes eligible for study: both
	Inclusion criteria: 18 years or older; sufficient command of the Danish language; have a personal code card (NemID)
	Exclusion criteria: no suicidal thoughts (defined as a cutoff score of <3 on the Beck Scale for Suicide Ideation)
Study type	Interventional
	Allocation: randomized
	Intervention model: parallel assignment
	Primary purpose: to lower the participant’s degree of suicidal thoughts
Date of first enrolment	August 2016
Target sample size	438
Recruitment status	Pending
Primary outcome(s)	Outcome: suicidal thoughts
	Method of measurement: Beck Scale for Suicide Ideation
	Time point: 2, 4 and 6 weeks after baseline, with time × group interaction test as indicator of efficacy
Key secondary outcomes	Suicidal thoughts, depression, hopelessness, worrying, quality of life, health care utilization, medication prescriptions, production loss, episodes of deliberate self-harm, death by suicide, negative effects of the intervention and evaluation and utility of the self-help program

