### Statistical methods

The null-hypothesis assumption is that there is no difference between the intervention and the control condition with respect to suicidal thoughts and the secondary outcome measures. Linear mixed models with repeated measurements and an unstructured covariance matrix, will use measurements at baseline, 2, 4 and 6 weeks (post test) with the purpose of modeling changes over time in suicidal thoughts. Mixed models will also be used to assess the long-term effect at 6 months after post test as well as the effect on the participant’s level of depression. This analytical approach handles missing data appropriately using maximum likelihood, under the assumption that data are not missing-not-at-random. The analytical models will include baseline values and stratification variables. Changes in other secondary outcomes will be measured using ANCOVA with multiple imputations. The imputation models will be linear regression for scale variables and binary logistic regression for dichotomous variables. Imputation models will be constructed separately for each randomization group, and include baseline values of the scales in question, stratification variables, variables predicting missing data, and potential auxiliary variables identified for each outcome. Analytical models will include the stratification variables. Robustness of analyses using multiple imputations will be tested using sensitivity analyses instead, replacing missing data with either very low or very high scores for scale variables, and all 0s or all 1s for dichotomous data. Since no missing data are present for register data, imputations will not be necessary for these analyses. Cohen’s *d* test will be used to determine the difference between the intervention and the control condition. In addition, incidence rates of deliberate self-harm will be calculated using a self-report questionnaire and hospital records. A cost-effectiveness analysis will be conducted based on the health care utilization and productivity levels of the observed participants. Lastly, the participant’s evaluation, usage and experience of negative effects during the intervention will be calculated and described.

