### Sample size

The sample size was estimated based on the expected effect on suicidal thoughts at 6 weeks. In the Dutch trial, the pooled standard deviation at post test was 0.9 and an effect size of 0.28 (Cohen’s *d*) was observed. If the true difference in mean scores of the intervention and the control condition is 0.30 in the Danish trial, 175 participants in each condition are needed to reject the null hypothesis that there is no difference between the intervention and the control condition at post test on suicidal thoughts with probability (power) 0.8. The type I error probability associated with this test of the null hypothesis is 0.05.

Approximately 90% of participants in the Dutch trial completed all post-test questionnaires. Accounting for a dropout rate of 20%, a total of 438 participants will be needed.

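### The primary test is stated in two incompatible ways: a group difference at 6 weeks, and a time × group interaction over weeks 2, 4 and 6; the 80% power was computed only for the first

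*Protocol article*

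**What the plan says.** Three places in the protocol article bear on which test decides the trial.

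- **Design, primary hypothesis:** the intervention is "superior to the control condition in reducing suicidal thoughts using the Beck Scale for Suicide Ideation at post test (6 weeks"). This is a group difference at one visit.
- **Sample size:** "The sample size was estimated based on the expected effect on suicidal thoughts at 6 weeks". The participants are needed "to reject the null hypothesis that there is no difference between the intervention and the control condition at post test on suicidal thoughts". This is the same single-visit comparison.
- **Design, Table 1, primary outcome:** the measure is the BSS, but the entry continues "Time point: 2, 4 and 6 weeks after baseline, with time × group interaction test as indicator of efficacy". This is a test across visits.

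Statistical methods gives the model but no deciding contrast. The linear mixed model with unstructured covariance "will use measurements at baseline, 2, 4 and 6 weeks (post test) with the purpose of modeling changes over time in suicidal thoughts", and "The analytical models will include baseline values and stratification variables". The first phrase suggests that baseline is a level of time; the second suggests that it is a covariate.

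The Abstract words the outcome differently again: "The primary outcomes are frequency and intensity of suicidal thoughts". The Primary outcome measure section names one outcome, the BSS total from 0 to 38.

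**The concern.** A group difference at 6 weeks and a time × group interaction answer different questions. The first asks whether the arms differ at post test. The second asks whether the difference between arms changes over the visits in the model. Either can be significant without the other.

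The interaction also means different things depending on baseline. If baseline is only a covariate and the visits are weeks 2, 4 and 6, a benefit that is present by week 2 and then holds steady produces no interaction. If baseline is a time level, the same benefit does produce one, because the arms start equal and then separate.

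What is at stake is which result decides the trial. The participants are not blinded and the primary outcome is self-reported, so the deciding test should be unmistakable in advance. The sample-size justification also covers only one of the two tests.

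**Working it through.** **Reproducing the plan's figure.** Inputs from Sample size: effect 0.30, power 0.80, type I error 0.05, dropout 20%. Reading 0.30 as a standardized difference and the test as two-sided:

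n per arm = 2(1.960 + 0.842)² / 0.30² = 174.4, rounded up to 175. With dropout, 175 / 0.80 = 218.75, rounded up to 219 per arm, or 438 in total. Power at 175 per arm is 0.801. The stated figures reproduce for a two-group comparison at one visit, with no interaction in the calculation.

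**Set-up for comparing the tests.** n = 175 per arm and unit SD at each visit. The document gives no correlation or trajectory, so both are assumed: compound symmetry (CS) or AR(1) with ρ from 0.5 to 0.8. The arm differences have covariance (2/n)Σ. A Wald test of contrasts C on differences δ has noncentrality λ = (Cδ)ᵀ[C(2/n)ΣCᵀ]⁻¹(Cδ), and power comes from the noncentral chi-square. When baseline is a covariate, Σ is the covariance of weeks 2, 4 and 6 given baseline.

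**Worked case, CS with ρ = 0.5.** Under CS the interaction noncentrality reduces to λ = n·SS / [2(1 − ρ)]. SS is the sum of squared deviations of the arm differences from their mean over the visits tested. Here λ = 175·SS.

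- Adjusted 6-week contrast, 1 df: λ = 0.30² / [(2/175)(1 − 0.5²)] = 10.5; power 0.90.
- Linear build-up (0.10, 0.20, 0.30), baseline as covariate, 2 df: SS = 0.02, λ = 3.5; power 0.37.
- Linear build-up, baseline as response (0, 0.10, 0.20, 0.30), 3 df: SS = 0.05, λ = 8.75; power 0.70.
- Constant 0.30 from week 2, 2 df: SS = 0, λ = 0; rejection rate 0.05, the type I error.
- Constant 0.30 from week 2, 3 df: SS = 0.0675, λ = 11.8; power 0.83.
- Transient effect (0.30, 0.15, 0), 2 df: SS = 0.045, λ = 7.9; rejection rate 0.71.
- Transient effect, 3 df: SS = 0.0619, λ = 10.8; rejection rate 0.80.

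**Range over CS and AR(1), ρ = 0.5, 0.6, 0.7, 0.8.** The adjusted 6-week contrast, for a difference of 0.30 at week 6, has power 0.81 to 0.997. The interaction with categorical time rejects as follows:

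| True pattern (weeks 2, 4, 6) | 2 df, baseline as covariate | 3 df, baseline as response |
|---|---|---|
| Linear build-up to 0.30 | 0.28–0.76 | 0.40–0.985 |
| Constant 0.30 | 0.05 | 0.70–0.998 |
| Late onset (0, 0.15, 0.30) | 0.57–0.98 | 0.50–0.996 |
| Transient (0.30, 0.15, 0) | 0.57–0.98 | 0.77–0.996 |

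In the last row there is no difference at week 6, so the primary hypothesis in Design is false. The Table 1 rule would still usually indicate efficacy.

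**The case against.** The strongest reply is that the narrative text is consistent. The hypothesis and the sample size both point to 6 weeks, and the conflicting line sits in a table of registration entries. On this view the article is a condensed account, and time coding and the role of baseline belong in a full protocol or analysis plan that is not shown. That is fair for the parameterisation, which alone would be no finding. It does not remove the conflict: the article itself names an efficacy test in Table 1 that differs from its hypothesis and sample size.

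Several stronger readings are tempting and should not be drawn.

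- A reader might infer that the interaction test lacks the stated power. The documents do not support this, since power depends on an unstated correlation, trajectory and role of baseline. Several cells of the table exceed 0.80, including late onset under the 2-df version at higher correlations. What can be said is that 80% is not shown for this test and may be far lower.
- A reader might infer that the interaction would miss a constant benefit. That holds only if baseline is a covariate and not a time level. Statistical methods lists baseline among the measurements, so the other reading is open, and power is then 0.70 or more.
- Multiple degrees of freedom are themselves an assumption, because an unstructured covariance does not make time categorical in the mean model. With linear time and baseline as a response, the 1-df interaction has power 0.56 to 0.997 for a linear build-up. It rejects in only 0.06 to 0.11 of trials for the transient pattern.
- The Abstract's mention of frequency and intensity might be taken as a third primary test. It is loose wording: Design, Table 1 and Primary outcome measure all name the BSS alone.
- A post hoc choice of result cannot be established from this article. An unseen analysis plan may fix the contrast.

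**Conclusion.** The point holds as an inconsistency about which test decides the trial. Design and Sample size rest on the 6-week BSS difference, Table 1 on a time × group interaction, and Statistical methods does not choose between them. The 80% power applies to the 6-week comparison only.

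The practical gap between the tests ranges from negligible to decisive. The 6-week contrast keeps at least about 81% power in every setting tried, whereas the interaction runs from 5% to nearly 100% for patterns that all reach 0.30 at week 6. Under either categorical-time version it can also be significant with no difference at week 6. These figures assume 175 completers per arm, a standardized effect of 0.30, equal SDs and correlations of 0.5 to 0.8; the document gives no correlations. The contradiction itself needs none of these assumptions. It should be corrected, because it concerns the result on which the trial is judged.

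**What to change.** Name one primary test and use it in Table 1, Design and Statistical methods: the model-based adjusted mean difference in BSS total score at 6 weeks, with 95% confidence interval and two-sided p-value, from the mixed model. This matches the existing hypothesis and sample size. State whether baseline is a response or a covariate in that model. Make the time × group interaction and the week-2 and week-4 contrasts supportive. As a minor correction, align the Abstract's outcome wording with the single BSS outcome.

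The cost is an edit to the protocol wording and an update of the registry entry where it carries the same text. No new data and no change in sample size are needed.

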### Sample and recruitment

The target population is adults in Denmark with suicidal thoughts. The study will be announced on The Lifeline’s website, and their volunteers will inform users about the study and refer to the web page listing where the study is described. Psychiatric hospitals and other outpatient clinics of relevance in the Capital Region of Denmark will be provided with information on the project, and are encouraged to refer patients with suicidal thoughts to The Lifelines website. See Fig. 1 for the trial flow diagram.

**Fig. 1 Fig1:**
[figure not shown]
Flow diagram for the Self-help Online against Suicidal thoughts (SOS) trial

### Eligibility criteria

To be eligible for enrollment, participants will have to: (1) be 18 years or older, (2) have a NemID, a personal code card used in Denmark for digital communication with authorities and (3) be fluent in Danish. Participants will be excluded from the study if they (1) do not provide their own telephone number and the telephone number of a contact person or (2) if no suicidal thoughts are noted (defined as a cutoff score of <3 on the Beck Scale for Suicide Ideation).

### Randomization

After filling out the baseline questionnaires, the participants will be randomized to the intervention or control condition using a centralized and computer-based algorithm with a hidden sequence. The algorithm is not accessible or known to the researchers directly involved in the project. The randomization is stratified by sex and level of suicidal ideation (using a cutoff score of ≥16 points on the Beck Scale for Suicide Ideation). A 1:1 allocation ratio will be applied.

### Intervention

Participants assigned the intervention condition will receive a Danish translation of the Dutch intervention, “Living under control” [7].

The intervention and its theoretical background has been described in detail elsewhere [9–11]. It consists of six modules that each takes a week to complete [7]. Every module starts with a theoretical section followed by one compulsory exercise, several optional exercises and a Frequently Asked Questions section. The participants are encouraged to use a minimum of 15 min twice a day to carry out the exercises and they can, through a message system on the website, write to the trial manager if they have any questions or concerns. It is up to each participant if they want to receive any help from the trial manager or just want to go through the intervention without any guidance.

The first of the six modules aims to help the participants to gain more control over their suicidal thoughts. Participants will be encouraged to schedule specific “worry times” during the day, e.g., 8 a.m. and 8 p.m., where they force themselves to think about all the things that upset them. The participants will be asked to perform this exercise every day for the 6 weeks that the intervention lasts. They will also be asked to tally every time they have a suicide-related thought as a means to be more conscious about their thoughts and how often they think about suicide.

In the second module, the participants will develop a crisis plan and practice how to tolerate intense emotions. The third module focuses on how participants can influence their feelings by being aware of negative thoughts. In the fourth module, the participants will be introduced to negative thinking habits and how these might influence thoughts and feelings. In the fifth module, the participants will be offered exercises aimed to help them reformulate negative thoughts. The last module focuses on the future and will help the participant make a relapse prevention plan.

Access to subsequent modules will be available on a weekly basis; e.g., when starting the intervention only the first module is available and the following week the second module will open. The participants in the intervention condition will also have access to the intervention after the first 6 weeks have passed. At the first login to the website, the personal code card, the NemID, is required; after this, participants will be able to choose a username and password. An authorized translation of the intervention into Danish was adapted by an experienced psychologist within the field of suicide prevention and the trial manager.

#### Waiting list

The participants in the control condition will have access to the SOS trial website but not to the modules or the message system. They can access an “Acute Help” page where they can seek help information, and a “My Profile” page where they can read the Informed Consent Form, the participant information and change their login and contact details (these features are also available to the participants in the intervention condition). Once the 32 weeks have passed, the first module of the intervention will be accessible for the participants in the control condition.

All participants can seek help and treatment during the trial. In material and messages with information about the study, the participants are furthermore encouraged to contact The Lifeline or their general practitioner if they are not feeling well.

